### The present study

The current study will investigate the processing of non-anomalous, simple sentences with differing word orders. The focus will be on the critical point in time, which is mainly the verb, but other regions of the sentence (such as NP2) will be investigated to check for spill-over effects.

The two conditions to be included are the active and the passive. The materials will be typical, plausible, reversible (both noun phrases are animate), violation-free sentences. There are some aspects of the Indonesian language that make the topic of the present study worth pursuing. First, the thematic roles of the NPs are coded by the passivization prefix on the verb rather than by case marking on the NPs. Second, unlike the studies of German [12] and Basque [19], no ambiguity manipulations are involved. Third, the structures to be tested in the current study are both relatively frequent compared to the passive structures in previously studied languages and are considered to be typical. The object-first conditions in the previous studies are infrequent in the respective languages compared to their subject-first counterparts; for example, the object-embedded relative clause in English [26] and the object-subject structure in German [27] are both highly infrequent structures. While arguments against exclusively syntactic frequency-based accounts of sentence processing have been established for German [28], there is behavioral evidence of the influence of sentence-level frequency and its interaction with other syntactic contrasts, such as the lexical bias of verbs [29–31].

The current experiment will contribute by providing electrophysiological data from Standard Indonesian, a zero-marking language that lacks many morphosyntactic features of Indo-European languages, paired with a relatively rigid word order. To the best of our knowledge, no ERP study has investigated Indonesian, where the ‘non-canonical’ sentence structure is relatively frequent. This is important because all the previous studies have compared one common sentence structure to an extremely infrequent one, and there is a wealth of evidence suggesting that syntactic frequency plays a role in sentence processing at the behavioral level [2, 32, 33].

The outcome of the proposed experiment will reveal the neural correlates of thematic role assignment, which is a common process in sentence processing. The proposed study will attempt to determine *whether there are neural correlates at all* for thematic role processing of non-anomalous sentences and will reveal potential underlying cognitive processes required to parse sentences.

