Other studies which have investigated thematic role assignment processing through ERPs included Meltzer and Braun [10], who compared the processing difference between subject-embedded and object-embedded relative clauses in English, and they found a negativity at NP1 (400-800ms) and a positive shift at the offset of the relative clause for reversible clauses. Jackson, Lorimor, & van Hell [15] observed positivity at the 500-700ms time window when comparing English passive structures to active structures; this positivity was strongest at the left anterior electrodes. In a study of Japanese, Wolff, Schlesewsky, Hirotani, and Bornkessel-Schlesewsky [16] included sentences that were similar to those in German, in which the object-first structures were compared to subject-first structures via the use of a suffix in the nominative or accusative case on the NP. ERPs for object-initial compared to subject-initial structures after NP1 included an early (120-240ms) negativity, which was referred to as ‘scrambling negativity’, a broadly distributed positive shift at the NP1 of Object-Subject structures (400-650ms), an N400 at the NP2 for Subject-Object structures, and a late parietal negativity (650-1050ms) at the verb. Aside from the object scrambling, the positive shift at the NP1 in object-initial sentences was interpreted as the resolution of dependency introduced by an accusative-first argument. Another study on Japanese [17] investigated how context usage influences processing of object-first structures. They observed that object-first structures elicited a sustained LAN at NP1 and P600 at NP2 when the NP1 was new and not provided in the context.

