The materials will be presented visually and word-by-word for 500ms with a 100ms blank screen between each word. Each trial begins with a blank screen of 750ms followed by the word ‘*siap*?’ (ready?), which stays on the screen until participants presses any keys. There will be two lists of sentences each pseudorandomized into 10 sets (each set containing 10 experimental sentences and 20 fillers). Digital triggers will be manually inserted at three time points in every sentence: at the onset of the verb (i.e., the onset of the prefix), and at the onset of NP2. Additionally, NP1 data points will be extracted from -1400 to -200 before the verb onset to be used as a sanity check to see if there are baseline differences between the conditions. It is important to note that the triggers will be located in the middle of the sentence.

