The EEG data will be re-referenced to the two mastoid electrodes. The ERPs will be calculated per participant, per electrode, and per condition in intervals of 200ms before onset to 1000ms after onset for each time-locked trigger. These epochs will then be demeaned per channel in each epoch (the mean of the data from the entire epoch will be subtracted from each data point, as this may result in better ICA decompositions than baseline-correcting based on pre-stimulus interval; [40]. The epochs will then be subjected to an independent component analysis using the runica() command in EEGLAB [41]; this will divide the data into many independent components corresponding to the number of channels, excluding mastoid electrodes, EOGs, and bad channels that are previously marked. These components will be inspected visually to identify blinks and saccades, and components that are identified as blinks or saccades will be removed (a maximum of four components per participant can be removed, and if the number of components removed exceeds this, the participant will be excluded from the analysis). After the removal of components corresponding to blinks and saccades, baseline correction will be applied to the data with a 200 ms pre-stimulus onset baseline. Next, the epochs will be run through a moving window peak-to-peak threshold function for artefact detection; epochs with artifacts will be marked for removal based on this criterion. Lastly, the data will be filtered using a 0.1–40.0 Hz bandpass filter via the pop_eegfiltnew() default EEGLAB function.

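### In the Table 2 layout the last 200 ms of the word after the verb is never tested and is also the NP2 baseline, yet the null conclusion rests on the verb and NP2 alone

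*Protocol article*

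**What the plan says.** The section The present study makes the verb the main region and adds that "other regions of the sentence (such as NP2) will be investigated to check for spill-over effects".

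Materials states that words are "presented visually and word-by-word for 500ms with a 100ms blank screen between each word". It announces that "Digital triggers will be manually inserted at three time points in every sentence", but the list that follows has two entries: "at the onset of the verb (i.e., the onset of the prefix), and at the onset of NP2". NP1 is then described as an additional extraction, cut by offset from the verb trigger (-1400 to -200 ms) as a check for baseline differences.

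Table 2 places an adjunct (*langsung*) between the verb and NP2, and it is the same word in both example rows. NP2 begins with *seorang* in the active row and *oleh* in the passive row.

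EEG recording and preprocessing sets epochs "in intervals of 200ms before onset to 1000ms after onset for each time-locked trigger", with a 200 ms pre-onset baseline. The Statistical analysis plan section tests all scalp electrodes over the whole post-stimulus part of the epoch.

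Predictions expects a passive positivity at 500-700 ms for the verb and a passive negativity at 300-600 ms for NP2. Its third prediction reads an absence of effects at both the verb and NP2 as a sign that earlier findings were confounded by syntactic frequency.

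**The concern.** The adjunct is the first place where an effect triggered by the verb prefix could spill over. In the example it is also lexically matched across conditions, which NP2 is not. The verb epoch stops before the adjunct ends, and the NP2 epoch takes its zero level from the remainder.

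Two things are at stake. First, a difference confined to that interval is never tested. Second, the same difference is removed from every NP2 sample by baseline correction, so the NP2 result depends on it. The protocol discusses distorted mid-sentence baselines and decides to keep the 200 ms baseline, but the only baseline check it names concerns NP1 and says nothing about the interval before NP2.

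Both problems bear on the third prediction. They can contribute to a false null at NP2, and they can also produce a false NP2 effect.

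**Working it through.** **Inputs.** Display 500 ms and blank 100 ms (Materials); epoch -200 to +1000 ms and 200 ms baseline (EEG recording and preprocessing); word order NP1, *itu*, verb, one-word adjunct, NP2 (Table 2); expected windows 300-600 ms and 500-700 ms (Predictions).

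**Step 1: reproduce the plan's own figure.** Onset interval = 500 + 100 = 600 ms. NP1 is two words before the verb, so its onset is -2 × 600 = -1200 ms. Its epoch is -1200 - 200 = -1400 ms to -1200 + 1000 = -200 ms. This equals the stated NP1 window and confirms the 600 ms interval.

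**Step 2: place the later regions (times from verb onset).**

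| Region | From | To |
|---|---|---|
| Verb test window | 0 | 1000 |
| Adjunct slot | 600 | 1200 |
| NP2 baseline | 1200 - 200 = 1000 | 1200 |
| NP2 test window | 1200 | 2200 |

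- Adjunct time inside the verb test: 1000 - 600 = 400 of 600 ms (67%).
- Adjunct time in neither test window: 1200 - 1000 = 200 of 600 ms (33%), which coincides with the NP2 baseline.

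**Step 3: illustrate with the protocol's windows, moved to adjunct onset.** The protocol predicts no adjunct effect, so applying these windows to the adjunct is an assumption.

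| Adjunct-locked window | From verb onset | In verb test | In NP2 baseline | In NP2 test |
|---|---|---|---|---|
| 300-600 ms | 900-1200 | 100 ms | 200 ms | 0 ms |
| 500-700 ms | 1100-1300 | 0 ms | 100 ms | 100 ms |

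**Step 4: effect on NP2.** Let D(t) be the passive-minus-active difference before the NP2 correction. The corrected NP2 difference is D(t) - mean(D over verb +1000 to +1200 ms).

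- If D equals d throughout the baseline and persists into NP2, the corrected value is d - d = 0. The effect is hidden.
- If D equals d in the baseline and returns to zero at NP2, the corrected value is 0 - d = -d. The effect appears reversed.
- If D equals d only over verb +1100 to +1300 ms, the baseline mean is d/2. NP2 shows +d/2 for its first 100 ms and -d/2 afterwards.

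The second case matters for the stated predictions. A passive positivity that began at the verb, lasted to +1200 ms and then faded would appear at NP2 as a passive negativity, which is the direction predicted there.

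**Step 5: sensitivity to adjunct length.** With a two-word adjunct (assumption), NP2 starts at 600 + 2 × 600 = 1800 ms. The interval in neither test window grows to 1800 - 1000 = 800 ms, and the NP2 baseline moves to 1600-1800 ms.

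**The case against.** The best defence is that most of the adjunct is tested and that the choice of regions is a design preference. The cluster test spans the whole post-stimulus epoch, so 400 of the adjunct's 600 ms are covered with a pre-verb baseline, and a sustained effect would probably show there. The windows predicted for the verb and NP2 lie fully inside their own epochs. These points stand, and they limit the problem to the 200 ms gap and its role as baseline.

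Three stronger readings are tempting but unsupported:

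- A reader might infer that the adjunct is missed altogether. It is not: its first 400 ms are tested.
- A reader might infer that it is never time-locked. The text announces three triggers and names two, and NP2 is introduced only as an example of the other regions. The third trigger may or may not be the adjunct.
- A reader might infer that the verb epoch cuts off the late effect reported for Japanese, because the introduction cites "a late parietal negativity (650-1050ms) at the verb". Table 1 gives 650-1000 ms for the same study, which fits the epoch completely. Even at 1050 ms only 50 of 400 ms would be lost.

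The adjunct's identity across conditions and its one-word length are likewise shown for one example pair only; the full item list is in an appendix that is not at hand.

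What the defence does not answer is the overlap of the untested interval with the NP2 baseline, or the use of NP2 as one of only two supports for the null conclusion when its first word differs by condition in the example.

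**Conclusion.** The concern holds in a limited form. For the layout in Table 2, 200 ms of the adjunct falls in neither the verb nor the NP2 test window and sets the zero level for NP2. A late or sustained voice effect there could be missed, masked or reversed, so nulls at the verb and NP2 alone are a weak basis for the third prediction. An NP2 difference is also harder to read, because it may reflect *seorang* against *oleh* or a shifted baseline.

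This rests on the fixed 600 ms interval, which the NP1 window confirms, on a one-word adjunct as in the example, and on the third trigger not being the adjunct. If the third trigger is the adjunct, the gap in testing may close. The NP2 baseline problem remains under the stated pre-onset baseline. The size of any contamination cannot be computed, because it depends on an effect that the documents do not quantify.

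**What to change.** 1. State what the third trigger is, or correct the count.
2. Extend the verb-locked epoch and cluster test, with the pre-verb baseline, through the adjunct to NP2 onset: verb +1200 ms for a one-word adjunct. The segment can be cut from the continuous EEG by offset, as is already planned for NP1. If adjunct length varies across items, say so and fix the common end point in advance.
3. Report the active-passive difference over verb +1000 to +1200 ms, on the pre-verb baseline, as a check on the NP2 baseline.
4. Treat anything beyond +1200 ms as overlapping NP2. For example, an adjunct window of 0-1000 ms would run to verb +1600 ms, 400 ms into a region whose first word differs by condition in the example.
5. Require the extended window also to be null before the third prediction is invoked.
6. If a separate adjunct test is added instead, control the error rate across regions. For independent tests at an assumed 0.05 each, the familywise rate is 1 - 0.95² = 0.098 for two and 1 - 0.95³ = 0.143 for three. A pre-adjunct baseline would fall at verb +400 to +600 ms and overlap the expected 500-700 ms verb effect by 100 ms, so the pre-verb baseline is safer.

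**Cost.** No new data. The verb search window grows from 1000 to 1200 ms (20%), which may slightly reduce sensitivity, and the longer segment will lose slightly more epochs to artefact.

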## Abstract

Previous studies of multiple languages have found processing differences between patient-first and agent-first word orders. However, the results are inconsistent as they do not identify a specific ERP component as a unique correlate of thematic role processing. Furthermore, these studies generally confound word order with frequency, as patient-first structures tend to be infrequent in the languages that have been investigated. There is evidence that frequency at the sentence level plays a significant role in language processing. To address this potential confounding variable, we will test a language where the non-canonical sentences are more frequent and are comparable to the canonical sentences, namely Standard Indonesian. In this language, there is evidence from acquisition, corpus, and clinical data indicates that the use of passive is frequent and salient. One instance of this difference can be demonstrated by the fact that it has been suggested that frequency may be the reason why Indonesian-speaking aphasic speakers do not have impairments in the comprehension of passives, whereas speakers of other languages with aphasia often do. In the present study, we will test 50 native speakers of Indonesian using 100 sentences (50 active and 50 passive sentences). If the neural correlates of thematic role processing are not observed in the critical region of the sentence (the prefix of the verb), this would suggest that the previous results were indeed influenced by frequency, but if we find that specific ERPs are connected to the hypothesized syntactic operations, this would further reinforce the existing evidence of the increased cognitive load required to process more syntactically complicated sentences.

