### Some relevant properties of Standard Indonesian

Indonesian is a zero-marking language [20] without case or gender markings. Transitive verbs are usually only inflected for voice (active or passive), and there is no verb inflection for tense, aspect, or agreement. Indonesian has SVO word order [21]; however, the ordering of constituents can be flexible, and it is possible (although infrequent) for verbs to take the initial position. Chung [22] suggested that Indonesian belongs to a branch of the Austronesian language family that was originally verb-initial, as the passivized transitive, active-transitive, as well as intransitive verbs can take the 1^st^ position.

The usual transitive passive (5b) has the patient in the initial position. Examples of typical simple active and simple passive sentences are as follows:

5a) Simple active (agent-patient / SVO)
Perempuan    itu    **men**dorong    laki-laki    itugirl    the    **ACT**-push    boy    the‘the girl is pushing the boy’5b) Simple passive (patient-agent / OVS)
Laki-laki    itu    **di**dorong    (oleh) perempuan    ituboy    the    **PAS**-push    (by)    girl    the‘the boy is pushed by the girl’

The canonical sentence (5a) contains a verb with an active-transitive voice marking (*men-*). Likewise, the passive is expressed by the prefix (*di-*) on the verb in (5b), where ‘the boy’ is the patient of the action. Similar to English, the by-phrase is optional in the passive. In addition, the preposition (*oleh*) ‘by’ may be omitted when the agent is immediately adjacent to the verb (Cole & Hermon, 2008). As the current study observes the ERP distinctions between the simple active and the simple passive, it is also worth noting that the typical passive in Indonesian, unlike in most Indo-European languages, is highly frequent. It is acquired at a very early stage (around 2 years old; [23]) compared to English (4–5 years old), which can be attributed to its high input frequency of 28–35% in Indonesian, compared to 4–5% in English. This difference is also reflected in the written form: Only 9% of English verbs display passive morphology [24] compared to 30–40% of Indonesian verbs [25] having the passive marker ‘*di-*‘.

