### Materials

Participants will read stimuli comprising 100 semantically reversible active and passive sentences (see S1 Appendix in S1 File). Examples of which are shown in Table 2.

**Table 2 pone.0272207.t002:** Stimuli examples of each condition.

Condition	NP1	Art	VP	Adjunct	NP2	PP/RC
Active	Polisi	itu	menembak	langsung	seorang perampok	di malam hari.
	Police	that/the	**ACT**shoot	immediately	(a) robber	at night.
		(the/a) police immediately shoots (the/a) robber at night.				
Passive	Polisi	itu	ditembak	langsung	oleh perampok	di malam hari.
	Police	that/the	**PAS**shoot	immediately	by robber	at night
		(the/a) police is immediately shot by (the/a) robber at night				

The sentences involve an animate subject and object and are constructed while avoiding a plausibility bias. Word order is manipulated by using two structures: simple active and simple passive sentences. Based on previous studies on processing well-formed sentences, the contrast of interest is passive-active, and whether the effects of the word order persist. We will strive for active-passive pairing plausibility with the use of NP1 and NP2 that are plausibly reversible (i.e. each sentence should not be strongly biased to one interpretation due to the nouns used). Additionally, there will be 200 filler trials consisting of questions (e.g. What did the adventurer notice yesterday?) and cleft sentences (e.g. it is the boy who the girl is calling) to prevent the habituation of the participants. The task for both the experimental and filler sentences will be discussed in the Procedure. The stimuli will be tested for acceptability and prototypicality using an online survey method utilizing a Likert scale of 1 to 7 with a similar setup used by Jackson, Lorimor, & van Hell [15]. Assuming the materials are rated acceptable and plausible by raters, the materials will not be further edited.

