### Frequency

The main aim of this study is to essentially ‘control’ for the possible effect of frequency. It might not be feasible to manipulate the relative syntactic frequency of a structure in a language. However, at the lexical level, verb bias (or the frequency with which verbs appear in different structures) influences both production [35] and comprehension [36]. While most of the previous studies did not address this variable in their materials, one study by Jackson et al. [15] attempted this by using the progressive participle ‘-ing’ in English (which is less frequent than the simple active verb form and is somewhat comparable to the passive) in combination with the past tense instead of simple present active structures. This has two potential issues; the first is we interpret thematic role processing as the assignment of agent/patient role to the first/second noun phrase in the study, and the active voice has several verb forms such as the simple form in which the first noun phrase is the agent, and when considered as a collective as they should be, these occur more frequently than the passive form. The second issue is whether the additional progressive aspect information deviating from the canonical default of the simple present active compared to passive will elicit a different neural signal is unknown. In our study, we will attempt to control verb bias by incorporating verb pairs that fulfil either of the two criteria:

A verb with higher token frequency in its passive form compared to its active form.A verb with the same frequency class* for both the passive and the active form.

*Frequency class is a number assigned to a group of words whereby this number does not often change in different corpora. The calculation is as follows: The frequency of the most frequent word in the corpus is divided by the frequency of the specific word, and log base 2 of the result is rounded up to the closest whole number.

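### The aim of establishing whether neural correlates of thematic role assignment exist at all is wider than a passive-versus-active contrast can answer: a null leaves it open, and a positive result answers it only in part

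*Protocol article*

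**What the plan says.** **The aim.** The closing paragraph of The present study states that "The outcome of the proposed experiment will reveal the neural correlates of thematic role assignment, which is a common process in sentence processing". Its second sentence is softer, since it speaks of an attempt, but it asks in emphasised type whether there are any correlates at all "for thematic role processing of non-anomalous sentences and will reveal potential underlying cognitive processes required to parse sentences".

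**The process.** The Frequency section defines it: "we interpret thematic role processing as the assignment of agent/patient role to the first/second noun phrase".

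**Where roles are marked.** Some relevant properties of Standard Indonesian says "The canonical sentence (5a) contains a verb with an active-transitive voice marking" (men-) and gives the passive its own prefix (di-) in the same position. Table 2 shows the two verb forms, menembak and ditembak, in the same slot.

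**The comparison.** The present study: "The two conditions to be included are the active and the passive". Materials: "the contrast of interest is passive-active, and whether the effects of the word order persist". The Statistical analysis plan tests that difference alone, by switching the two labels at random within each participant.

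**Reading of a null.** The Abstract begins its null branch with "If the neural correlates of thematic role processing are not observed in the critical region of the sentence" and concludes that earlier results were influenced by frequency. The third item under Predictions likewise calls a null a lack of ERP correlates at the verb and NP2, and concludes that earlier findings were confounded by syntactic frequency.

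**The concern.** The aim is about whether a process has a neural correlate. The design measures whether two versions of that process differ. The two coincide only if one condition lacks the process, and neither does: in the active sentence NP1 becomes agent and NP2 patient, and in the passive the reverse. The article describes no tested condition without role assignment. NP1 data serve as a baseline check, and the fillers are there to prevent habituation.

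What is at stake is what the study may conclude. The article is a Registered Report Protocol, so its aims and readings are set before data are seen. If they stay as worded, a null could be taken as evidence on a question that the contrast does not address, and a positive result could be credited with revealing role assignment as such, not one differential part of it.

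**Working it through.** **Inputs**
- Two conditions and one contrast, passive minus active (The present study; Materials; Statistical analysis plan).
- Role assignment occurs in both conditions (definition in Frequency; prefixes in Some relevant properties of Standard Indonesian).
- A passive-only component: revision of NP1 from an assumed agent to patient (Predictions, first item).
- 50 participants, from doubling the 25 of an earlier study (Participants): 2 × 25 = 50, which reproduces. The argument does not depend on this figure.

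**Algebra**

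Let c be the response common to role assignment in both voices, and d whatever the passive adds.
- Active: c
- Passive: c + d
- Contrast: (c + d) − c = d, for every c

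d can itself be split as d = r + f, where r is the cost of revising NP1 to patient and f is any effect of the prefixes being different forms. The contrast gives r + f and carries no information on c.

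**The same holds for the planned test.** The cluster test works on within-participant differences, and switching labels only changes the sign of a participant's difference. Adding the same c to both voices, even a c that varies by participant, channel and time, leaves every observed and permuted difference unchanged. The p-value is therefore the same for any c.

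**Numerical illustration**

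Assumptions, none of them from the article: SD of the paired difference 1, one paired t-test at two-sided 0.05 in place of the cluster test, n = 50, 20,000 replicates.

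| Shared activity c | d = 0 | d = 0.4 | d = 0.5 |
|---|---|---|---|
| 0 | 5.2% | 79% | 93.5% |
| 2 | 4.7% | 80% | 93.2% |
| 5 | 5.1% | 79% | 93.5% |

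Entries are rejection rates. The Monte Carlo standard error near 5% is √(0.05 × 0.95 / 20,000) = 0.0015, so the first column varies only by simulation noise. Each column is flat in c. Across the rows, the contrast responds to d.

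**Reading each outcome against the aim**
- *Null:* compatible with c = 0 and with a large c alike. It does not bear on whether role assignment has a neural correlate.
- *Positive:* d is not zero. If f can be set aside, this supports r, which is one correlate of thematic role processing. It still does not measure c.

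**The case against.** The strongest reply is that the voices do not do the same work at the prefix. On the agent-first account in Predictions, the active confirms a role already given to NP1 and the passive revises it. That revision does not cancel, and it is the process of interest. This stands. A reader might infer from the cancellation that the aim cannot be met in any outcome; the article does not support that, because a positive contrast could support a reassignment correlate.

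A reader might also infer that the authors plan to report a null as absence of neural correlates of thematic role processing. They do not say so. The reading given in both the Abstract and Predictions is that earlier findings were confounded by frequency, and the wording about existence at all occurs only in The present study. Whether the frequency inference is itself sound is a separate matter.

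Third, the article's review of earlier work uses the term neural correlate for differences between word orders, so the aim may be shorthand for such a difference. This has some force, and the operative predictions are indeed differential. But the aim calls role assignment a common process and asks whether it has correlates at all, and the Frequency section defines the process as assignment itself. The review also declines to attribute a word-order P600 in Basque to thematic role processing, so the authors do not treat the two as the same thing.

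Finally, any two-condition subtraction has this property. That is true, and it is why the stated aim should match it.

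**Conclusion.** The concern holds in a limited form. The aim in The present study is broader than the design can deliver. Role assignment common to both voices is not identified, so a null cannot show that correlates are absent, and a positive result supports only a differential correlate, subject to the difference in prefix form. The size is all or nothing for c: none of it reaches the contrast, at any sample size. For d, the planned contrast is informative.

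The cancellation rests only on the article's definition of the process and its single contrast. The simulated rates rest on the assumed SD, effect sizes and significance level, and are illustrative. Nothing here faults the conditions, the test or the passive-versus-active predictions. It is a change of wording worth making before data are collected, because it alters what the study may conclude.

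**What to change.** - **The present study, closing paragraph:** state the aim as whether assigning the patient role to NP1 evokes a different response from assigning the agent role, in a language where both structures are frequent. Delete the phrase about correlates existing *at all*.
- **Abstract and third item of Predictions:** word a null as *no passive-active difference was detected*, and add that role assignment common to both voices is not measured.
- **Leave unchanged:** the passive-versus-active predictions for the verb and NP2, which are already differential.

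The cost is a narrower headline claim. Conditions, stimuli, sample size, exclusions and the permutation test are not affected.
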